# Trial Identifications

| TRIAL FULL TITLE | Verification of the Efficacy of a Non-invasive Game Therapeutic Intervention with “Specific Memory Attenuation” Effects to Alleviate PTSD Symptoms |
| --- | --- |

# Abbreviations and Definitions

| *AE* | *Adverse Event* |
| --- | --- |
| *SAP* | *Statistical Analysis Plan* |
| *ShIF* | *Shadow-induced forgetting* |

# Introduction

## Preface

Traumatic memories can be intrusively triggered by various factors in daily life, causing distress [1]. Therefore, providing a safe and effective method to weaken the pairing between trauma and its associated triggers is of paramount importance, particularly for individuals suffering from post-traumatic stress disorder (PTSD). This study assumes the existence of an object associated with the memory (e.g., a victim of assault by a person wearing a “yellow hoodie” may form a pairing between the “yellow hoodie” and the traumatic memory) and proposes a game-based process designed to weaken this object-memory association. The process can be summarized as presenting a cue associated with the memory to be weakened during a “Reverse Game” that reduces hippocampal activity. By playing the game and experiencing hippocampal activity reduction, the memory stored in the hippocampus is reactivated by presenting the associated cue during reduced hippocampal activity, thereby weakening the object-memory pairing.

This study is significant for two reasons:

1. It verifies the induction of memory attenuation using a game-based process that is not monotonous, thus suggesting the possibility of providing “enjoyable therapy” for trauma patients.
2. By verifying the effectiveness of both consciously perceivable (Conscious) and unconsciously perceivable (Unconscious) stimulus presentations during the “stimulus presentation” process, the study demonstrates that cues can be presented subliminally (preconsciously) to mitigate the intrusive nature often associated with trauma treatments.

## Purpose of the analyses

These analyses will assess the efficacy of a game process designed to induce memory weakening non-invasively, comparing it with a control group through a clinical study conducted on general college students.

# Study Objectives and Endpoints

## Study Objectives

(ICH E3; 8.)

The purpose of this study is to evaluate the effects of cue exposure conditions (Conscious, Unconscious, Control) on short-term and long-term memory suppression and to determine whether these effects are modulated by emotional valence (Positive, Negative).

Specifically, this study aims to:

1. Short-Term Effects: Assess the immediate impact of conscious and unconscious cue exposure on memory suppression compared to a control condition, using METEOR scores measured immediately after the intervention (Day 1).
2. Long-Term Effects: Investigate whether the suppression observed on Day 1 persists over time (Day 2, Day 4), reflecting long-term forgetting trajectories across exposure conditions.
3. Interaction with Emotional Valence: Determine whether the effects of cue exposure conditions differ for images with positive versus negative emotional valence, highlighting potential emotional modulation of memory suppression processes.
4. Neural Correlates: Explore the underlying neural mechanisms of memory suppression by analyzing EEG activity, focusing on comparisons between exposure conditions (Conscious vs. Unconscious) and valence (Negative vs. Positive) across key frequency bands (alpha, beta, theta, delta, gamma).

This comprehensive approach will provide insights into both the behavioral and neural dimensions of memory suppression, offering a deeper understanding of how cue exposure and emotional content influence forgetting processes.

## Endpoints

(ICH E9; 2.2.2)

1. Primary Endpoint

- Endpoint: Short-term memory suppression (METEOR scores).
- Definition: Memory suppression will be assessed using METEOR scores, a measure of semantic similarity reflecting accurate and context-rich recall.
- Time Point: Day 1 (immediately post-intervention).
- Comparisons:
- Cue exposure conditions: Conscious vs Control, Unconscious vs Control.
- Subgroup analysis: Positive vs Negative emotional valence.
- Hypothesis:
- Total Image Group: Conscious < Control, Unconscious < Control (one-tailed t-test).
- Negative Image Group: Conscious < Control, Unconscious < Control (one-tailed t-test).
- Positive Image Group: Conscious < Control, Unconscious < Control (one-tailed t-test).

2. Secondary Endpoints

- Endpoint 1: Long-term memory suppression (METEOR scores over time).
- Definition: Assessment of METEOR scores on Day 2 (24 hours post-intervention) and Day 4 (72 hours post-intervention) to evaluate memory suppression persistence.
- Time Points: Day 1, Day 2, Day 4.
- Analysis: Repeated paired t-tests (Conscious vs Control, Unconscious vs Control).
- Endpoint 2: Group differences in memory performance trajectories.
- Definition: Evaluation of memory decline over time using Difference-in-Differences (DID) analysis, adjusted for covariates such as: feedback Cycle Times (duration of self-feedback process during the learning phase), and frequency of Image Repetition (number of image viewings during the learning phase).
- Purpose: To supplement time-specific t-test comparisons and better understand group differences in forgetting trajectories.
- Endpoint 3: Emotional valence-based comparisons.
- Definition: Paired two-tailed t-tests comparing METEOR scores across valence conditions at each time point:
- Negative Treatment vs Positive Treatment
- Negative Conscious vs Positive Conscious.
- Negative Unconscious vs Positive Unconscious.
- Negative Conscious vs Positive Unconscious.
- Negative Unconscious vs Positive Conscious.

3. Exploratory Endpoints

- Endpoint: EEG-based neural activity analysis.
- Definition: Neural activity will be compared across cue exposure conditions and emotional valence groups using EEG power spectrum density.
- Frequency Bands: Alpha, beta, theta, delta, and gamma.
- Comparisons:
- Cue Exposure: Conscious vs Unconscious phases.
- Emotional Valence: Negative vs Positive image groups.
- Statistical Method: Two-tailed Wilcoxon signed-rank test for paired comparisons.

## Derived variables

1. Timepoint-Specific METEOR/Gist Score Comparisons

- Definition: A derived variable representing the differences in METEOR and Gist scores between groups (e.g., Control vs Conscious, Control vs Unconscious) at each assessment timepoint: Day 1, Day 2, and Day 4.

This variable allows for the evaluation of whether group differences persist, diminish, or change over time.

2. Timepoint-Specific METEOR/Gist Score Change

- Definition: A derived variable representing the within-group change in METEOR and Gist scores across the three assessment timepoints (Day 1, Day 2, and Day 4).

This variable is used to measure the progression or decline of memory performance over time for each group.

3. EEG-Based Neural Activity Comparisons

- Definition: A derived variable representing the differences in EEG power spectrum density across the following conditions:
- Cue Exposure Condition: Conscious vs Unconscious phases.
- Emotional Valence: Negative vs Positive image categories.

This variable enables the identification of significant neural activity differences associated with exposure conditions and emotional valence.

# Study Methods

## General Study Design and Plan

(ICH E3;9)

This study employs a **within-subject design**, where each participant serves as their own control. This design reduces inter-subject variability, allowing for more precise comparisons across conditions. The study evaluates the interaction between the following three factors, with participants learning a total of 36 cue-target image pairs, categorized as follows:

- **Exposure Condition:** Control, Conscious, Unconscious
- **Valence:** Positive, Negative
- **Test Timepoint:** Day 1 (immediately post-Gaming), Day 2 (24 hours post-Gaming), Day 4 (72 hours post-Gaming)

This factorial design facilitates the assessment of how exposure condition, emotional valence, and time influence memory performance (measured by METEOR scores) and neural activity (assessed through EEG). The within-subject approach ensures that each participant’s performance under one condition can be directly compared to their performance under other conditions.

## Inclusion-Exclusion Criteria and General Study Population

(ICH E3;9.3. ICH E9;2.2.1)

1. **Inclusion Criteria**

- Average corrected binocular visual acuity of 0.5 or higher.
- No notable health issues.
- Proficiency in Korean language.

1. **Exclusion Criteria**

- Participants whose feedback cycle times during the learning phase are too long or too short (outliers determined as those outside the interquartile range [IQR] of all participants’ distributions).
- Participants requiring more than 10 minutes to wear the EEG device are excluded from EEG analysis.
- Additionally, participants whose EEG data were poorly measured or recorded are excluded from EEG analysis.

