**Detailed Description of Variables**

1. Feedback cycle times (Learning phase) :

- Definition: The time participants take to process and respond to feedback during the learning phase
- Numeric Range: Recorded in seconds
- Exclusion Rule: Outliers defined as those outside the interquartile range (IQR) will be excluded from analysis.

1. The frequency of Image repetition (Learning phase):

- Definition: The number of times participants repeatedly viewed images during the learning phase.

1. METEOR Score (Memory Performance):

- Definition: Semantic similarity score reflecting accurate and context-rich recall of cue-target pairs.
- Numeric Range: continuous variables with no predefined range. Higher scores indicate greater semantic recall accuracy.
- Handling Missing Data: Missing scores will not be imputed.

1. Gist Score (Memory Performance):

- Definition: Percentage of core narrative elements (Gist items) accurately recollected from each scene, reflecting participants’ ability to recall essential story components.
- Numeric Range: expressed as percentages, with a theoretical range of 0% (no Gist items recollected) to 100% (all Gist items recollected).
- Handling Missing Data: Missing scores will not be imputed.

1. EEG Data (Neural Activity):

- Definition: Neural activity recorded during the gaming phase, segmented into 2-second epochs for analysis.
- Exclusion Rule: EEG data with significant artifacts (e.g., noise, poor electrode contact) will be excluded.

1. Adverse Event Monitoring:

- Definition: Documentation of any unexpected physiological or psychological effects during the study period.

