# Sample Size

(ICH E3; 9.7.2. ICH E9; 3.5)

The sample size for the study was determined to be 150 participants based on a prior study [2], which measured EEG activity in adult males to investigate the therapeutic effects of NF training.

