### Full Analysis Population

- All participants who completed the learning phase and provided at least one valid METEOR score or Gist score during the testing phases (Day 1, Day 2, Day 4).

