## Protocol Deviations

**1. Definition of Major Deviations**

Major deviations are defined as those that significantly affect the integrity of the data or the primary and secondary outcomes. Examples include:

- Participants whose feedback cycle times during the learning phase fall outside the interquartile range (IQR), indicating abnormal or inconsistent learning performance.
- Participants with significant EEG recording issues (e.g., excessive artifacts, technical failure) that result in unusable EEG data.
- Participants who failed to complete the gaming phase or any of the required assessments on Day 1, Day 2, or Day 4.

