**2. Impact on Analysis Populations**

- **Full Analysis Population (FAP):**
  - Participants with minor deviations (e.g., small timing discrepancies) will remain included.
  - Major deviations will not exclude participants from the Full Analysis Population.
- **Per Protocol Population (PPP):**
  - Participants with major protocol deviations (e.g., unusable EEG data, extreme feedback cycle outliers) will be excluded.

The summary statistics will be produced in accordance with section 9.

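### Feedback-time outliers are defined as anyone outside the interquartile range, which flags about half of the participants, and the SAP disagrees with itself on whether they leave the primary analysis

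*SAP*

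**What the plan says.** The cut-off appears three times in the SAP, each time as the interquartile range itself.

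- Section 5.2 lists it among the exclusion criteria, for times that are unduly long or unduly short: "outliers determined as those outside the interquartile range [IQR] of all participants". The two EEG criteria beside it are expressly limited to the EEG analysis. This one carries no such limit.
- Section 5.3, in the description of the feedback variable (recorded in seconds): "Outliers defined as those outside the interquartile range (IQR) will be excluded from analysis". It names neither participants nor an analysis population.
- Section 8.2, as an example of a major deviation: "Participants whose feedback cycle times during the learning phase fall outside the interquartile range (IQR), indicating abnormal or inconsistent learning performance".

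On the consequence for the analysis populations:

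- Section 7.2.1 defines the Full Analysis Population without any feedback-time condition: "All participants who completed the learning phase and provided at least one valid METEOR score or Gist score during the testing phases".
- Section 8.2 adds: "Major deviations will not exclude participants from the Full Analysis Population". For the Per Protocol Population it says: "Participants with major protocol deviations (e.g., unusable EEG data, extreme feedback cycle outliers) will be excluded".
- Section 8.1 gives excessive feedback-time deviations as an example of a reason for dropout.
- The Listing of Tables, Listings and Figures assigns the Full Analysis Population to every METEOR, Gist, DID and EEG table, including Table 4.1 (the Day 1 paired t-tests), and to all four figures. The disposition table has no population. No table or figure is assigned to the Per Protocol Population.

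**The concern.** There are two linked problems.

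**The cut-off.** The interquartile range is the middle half of a distribution. A rule that calls everything outside it an outlier flags the other half, whether or not any value is unusual. It would select people of middling learning speed, and would cut feedback cycle time, which section 7.3 makes a covariate in the DID analysis, to its central half.

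**The consequence.** Section 5.2 takes flagged people out, while sections 7.2.1 and 8.2 keep them in the Full Analysis Population. Nothing says which text governs. Because the quartiles come from the participants' own data and the analysis is run after Day 4, the number in the primary analysis could be settled after results are visible.

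**Working it through.** **Inputs.** Planned sample 150 (section 6). Primary test: paired t-test, one-sided, 5% level (section 9.1). Section 6 takes the 150 from a prior study and gives no effect size, SD, power or dropout, so the figure cannot be reproduced. The share flagged does not depend on it. Assumptions: all 150 contribute, with one continuous feedback time each. LQ and UQ are the lower and upper quartiles.

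**Step 1: share flagged as written.** P(X < LQ) + P(X > UQ) = 0.25 + 0.25 = 0.50 for any continuous distribution. Counting values outside the sample quartiles for n = 150 under eight quantile conventions gave 74 to 76 (74/150 = 49.3%; 76/150 = 50.7%). Simulation with the default convention gave 76 for normal and for lognormal data (log-scale SD 0.5 and 1). So 74 to 76 remain.

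**Step 2: comparison with a conventional fence.** If LQ − 1.5 × IQR and UQ + 1.5 × IQR had been meant (an assumption), the mean number flagged per 150 would be about 1.4 (normal), 5.9 (lognormal, SD 0.5) or 11.7 (lognormal, SD 1).

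**Step 3: illustrative power.** The effect below is back-solved from 80% power at 150 and is not a planned effect. By the normal approximation:

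- Detectable effect at n = 150: (1.645 + 0.842)/√150 = 0.203 SD of the paired difference.
- Detectable effect at n = 75: 2.487/√75 = 0.287. The noncentral t gives 0.204 and 0.290.
- Power at n = 75 for 0.203: Φ(0.203 × √75 − 1.645) = Φ(0.113), about 0.54 to 0.55. The noncentral t gives 0.54.
- Enrolment needed to keep 150 after a loss of half: 150/(1 − 0.5) = 300.

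**Step 4: would raw-scale 1.5 × IQR fences be a sufficient repair?** Times tend to be right-skewed (an assumption here).

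- Lognormal, SD 0.5, median 1: LQ = 0.714, UQ = 1.401, lower fence 0.714 − 1.5 × 0.687 = −0.32.
- Exponential, mean 1: LQ = 0.288, UQ = 1.386, lower fence 0.288 − 1.5 × 1.098 = −1.36.

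A time cannot be negative, so neither fence could flag an unduly short one, which section 5.2 wants to catch. On the log scale, the lognormal example has quartiles ±0.337 and IQR 0.674. The fences are ±(0.337 + 1.5 × 0.674) = ±1.349, or 0.26 and 3.85 on the time scale, so both tails can be flagged.

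**Step 5: the population texts side by side.**

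| Place | Effect on a flagged participant |
| --- | --- |
| 5.2 | Excluded, with no limit to one analysis |
| 5.3 | Outliers dropped from analysis; participant or value not stated |
| 7.2.1 | Kept in Full Analysis |
| 8.1 | May be counted as a dropout |
| 8.2 | Kept in Full Analysis, removed from Per Protocol |

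Section 5.2 and sections 7.2.1 and 8.2 cannot all be followed for the same person.

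**The case against.** The strongest reply is that nobody meant to drop half the cohort. The SAP speaks of outliers, of abnormal performance and of extreme cases, and none of these describes every second participant. The three statements may be one shorthand copied twice, with the multiplier lost. That is probably right. It explains the defect but does not remove it, because the text as it stands gives an analyst no other number to program.

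Several narrower points stand.

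- The half holds for one continuous value per participant. Section 5.3 does not say how a person's cycles become one value (section 9.2 speaks of a total duration for the DID covariate), and heavy ties at the quartiles would lower the share.
- Section 5.3 may refer to outlying values, so the firm conflict is section 5.2 against sections 7.2.1 and 8.2.
- The population sections and the table listing agree in keeping these people. On that route the loss falls only on the Per Protocol Population, for which no output is listed.

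A reader might infer that the plan discards half of the primary sample. The documents support that only if section 5.2, or section 5.3 read as excluding people, overrides section 8.2, and they do not say that it does. A reader might also infer a bias between exposure conditions. The feedback time is recorded before gaming and the design is within-subject, so an excluded person leaves all conditions alike. The cost is in precision, generalisability and analyst discretion.

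**Conclusion.** The point holds in this form. The stated cut-off flags about half of the participants (74 to 76 of 150), which does not match the SAP's own description of whom it should catch. The SAP also contradicts itself on whether those people stay in the primary analysis. Depending on which text is followed, that analysis has about 150 or about 75 participants. If section 8.2 governs, the primary analysis is intact and only the Per Protocol Population is halved, which would leave it a poor supporting analysis.

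The count rests on one continuous value per person and full participation. The power figures (80% to about 54%; detectable effect about 0.20 to 0.29 SD) are illustrations on an assumed effect and do not measure a shortfall against a planned power, because the SAP states none. The matter should be settled before analysis, since it decides who is in the primary comparison and is cheap to correct.

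**What to change.** 1. Name one per-participant summary of feedback cycle time. In sections 5.2 (if any mention remains there), 5.3 and 8.2, replace the bare interquartile-range wording with an explicit numeric fence, fixed before the data are seen, that can flag both tails. Fences at 1.5 × IQR on log-transformed times are one example; the multiplier and scale are for the sponsor to choose and justify.
2. Delete the rule from the exclusion criteria in section 5.2. It needs the learning-phase data of all participants, so it cannot work as an entry criterion. In section 5.3, limit the exclusion to the Per Protocol Population; changing the fence alone would leave the conflict with section 8.2.
3. State in section 9.1 that the primary analysis keeps all Full Analysis participants, as sections 7.2.1 and 8.2 and the table listing already imply. Reconcile section 8.1, so that a feedback-time deviation is not counted as a dropout when the participant stays in the analysis.
4. Add a Per Protocol sensitivity version of Table 4.1 that applies the fence.

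The cost is wording changes in these sections and one extra sensitivity table, with no new data or participants.

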## Study Variables

(ICH E3; 9.5.1. ICH E9; 2.2.2)

|  | Day1  (pre-gaming) | Day1  (Post-gaming) | Day2  (24 hours Post-Gaming) | Day 4  (72 hours Post-Gaming) |
| --- | --- | --- | --- | --- |
| Feedback cycle times (Learning phase) | x | - | - | - |
| The frequency of Image repetition (Learning phase) | x | - | - | - |
| METEOR Score (Memory performance) | - | x | x | x |
| Gist Score (Memory performance) | - | x | x | x |
| EEG data (Neural activity) | - | x | - | - |
| Adverse event monitoring | x | x | x | x |

**Time-Window Definitions**

- Day 1 Pre-Gaming: observation collected before the gaming phase
- Day 1 Post-Gaming: Assessments conducted immediately after the gaming phase.
- Day 2 and Day 4 Follow-Ups: Assessments conducted within a 2-hour window of the scheduled time (e.g., between 22–26 hours for Day 2). Measurements collected outside this window will be flagged as deviations and handled during analysis.

**Rules for Measurements Outside Scheduled Times**

- For EEG and METEOR Score data collected outside the specified time-windows, observations will be excluded unless determined by the investigator to be reliable for analysis.
- Missing EEG epochs or METEOR scores due to technical issues will not be carried forward; instead, the remaining valid observations will be analyzed.

**Detailed Description of Variables**

1. Feedback cycle times (Learning phase) :

- Definition: The time participants take to process and respond to feedback during the learning phase
- Numeric Range: Recorded in seconds
- Exclusion Rule: Outliers defined as those outside the interquartile range (IQR) will be excluded from analysis.

1. The frequency of Image repetition (Learning phase):

- Definition: The number of times participants repeatedly viewed images during the learning phase.

1. METEOR Score (Memory Performance):

- Definition: Semantic similarity score reflecting accurate and context-rich recall of cue-target pairs.
- Numeric Range: continuous variables with no predefined range. Higher scores indicate greater semantic recall accuracy.
- Handling Missing Data: Missing scores will not be imputed.

1. Gist Score (Memory Performance):

- Definition: Percentage of core narrative elements (Gist items) accurately recollected from each scene, reflecting participants’ ability to recall essential story components.
- Numeric Range: expressed as percentages, with a theoretical range of 0% (no Gist items recollected) to 100% (all Gist items recollected).
- Handling Missing Data: Missing scores will not be imputed.

1. EEG Data (Neural Activity):

- Definition: Neural activity recorded during the gaming phase, segmented into 2-second epochs for analysis.
- Exclusion Rule: EEG data with significant artifacts (e.g., noise, poor electrode contact) will be excluded.

1. Adverse Event Monitoring:

- Definition: Documentation of any unexpected physiological or psychological effects during the study period.

